## **2.6 Summary of the foreseeable and known benefits and risks for research participants**

The expected adverse events during the SARS-CoV-2 screening practice from a nasopharyngeal sample are:

1. the appearance of discomfort or cough when the nasopharyngeal sample is taken,
2. the need to redo the test if it is invalid or read outside the time limits or if it must be confirmed.

Risks for people can be considered minimal.

Nurse screening for SARS-CoV-2 could become a common practice during the pandemic period in emergency services if it is shown that its implementation makes it possible:

1- to screen for the pauci or asymptomatic forms of SARS-CoV-2 infection that can escape other screening schemes, and thus contribute to the reduction of the active cycles of infection,

2- to quickly confirm or refute the Covid-19 diagnosis in people with respiratory symptoms (syndromic diagnosis),

3- to limit the risks of transmission of persons tested positive through the immediate and direct activation of the COVISAN scheme to support the isolation of persons who are not hospitalised (conveying isolation measures/reduction of transmission risks), the search for contact cases by home testing of household members and the search for the source by questionnaire,

4- to analyse the exposure factors in persons tested positive using the DEPIST-COVID questionnaire, as well as to accompany participation in the ComCor study of the Pasteur Institute to evaluate the sociodemographic, behavioural factors and practices associated with SARS-CoV-2 infection and to compare the characteristics of positive patients in three schemes: DEPIST-COVID, ComCor and COVISAN,

5- to monitor the community spread of the SARS-CoV-2 virus in the Paris Metropolitan area on a sample of individuals consulting in emergency departments and not on biased voluntary testing, as well as to estimate by modelling the incidence of new SARS-CoV-2 infections and the public health benefit of the testing process.

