#### 3.2 Secondary objectives of the research

The secondary objectives are:

- To compare the proportion of SARS-CoV-2-positive patients among asymptomatic patients tested to that of the Paris Metropolitan area during the same period (the comparison will also be made by geographical area of each emergency department, and among the symptomatic patients tested and among the entire tested population),
- Evaluate the feasibility of the screening strategy,
- Describe patients tested and positive for SARS-CoV-2 in both periods:
  - o Describe the proportion of positive tests,
  - o Describe the proportion of asymptomatic patients among tested patients and among patients tested positive for SARS-CoV-2,
  - o For the symptomatic patients tested positive: describe the symptomatology,
  - o Describe the patient exposure factors according to the SARS-CoV-2 test result with the help of the DEPIST-COVID questionnaire,
- Describe sociodemographic and behavioural factors and habits associated with SARS-CoV-2 infection in patients tested in one of the following three schemes: DEPIST-COVID (positive cases and negative controls), ComCor and COVISAN,
- Estimate the incidence of new SARS-CoV-2 infections in the Paris Metropolitan area: proportion of positive patients and their profiles. Estimate the under-detection of cases in the region, and compare with results from the model experiment,
- Estimate the number of close contact persons who have been tested for SARS-CoV-2 and who have isolated over both periods.

An ancillary study will focus on the evaluation of rapid SARS-CoV-2 detection techniques in asymptomatic patients, in particular rapid antigen testing (RAT) and rapid molecular testing (RT-LAMP), compared to a reference technique, RT-PCR (see § 10. Ancillary study).

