### 4 RESEARCH DESIGN

#### 4.1 Primary outcome

The primary outcome is: the proportion of patients tested positive for SARS-CoV-2 amongst the flow of consulting adults.

It is important to note that the denominator is a number of patients in the emergency departments and not the number of tests performed.

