#### 4.2 Secondary endpoints

The secondary evaluation criteria are:

1. Compare the proportion of patients tested positive for SARS-CoV-2 amongst asymptomatic patients tested in the Paris Metropolitan area in the same period, as well as in the geographical area of each ED,  
(the proportion of patients positive for SARS-CoV-2 among the symptomatic patients tested and among the entire population tested will also be noted in the study, as well as within the Paris Metropolitan area and in each geographical area of the EDs),
2. Proportion of patients who have completed the questionnaire, proportion of offered, accepted and performed tests, and notified of the SARS-CoV-2 result and staff involved (nurses, caregivers, doctors, others),
3. Proportion of patients who have tested positive for SARS-CoV-2 in both strategies (positive tests),  
Proportion of asymptomatic patients among the patients tested and among the patients tested positive in the 2 strategies,  
For symptomatic patients who have tested positive in the 2 strategies and the total population: description of the symptomatology,  
Patient exposure factors in the two study strategies and according to the result of the SARS-CoV-2 test using the items in the DEPIST-COVID questionnaire,
4. Sociodemographic, behavioural factors, and practices associated with SARS-CoV-2 infection in patients tested in 3 schemes: DEPIST-COVID (positive cases and negative controls matched on age, sex and area of residence in the last 10 days), ComCor and COVISAN,
5. Estimate of incidence in the region, estimate of under-detection of cases in the region, and comparison with results from the model experiment,
6. Number of close contact persons who have been tested, positive for SARS-CoV-2 and isolated over both periods.

An ancillary study will focus on the evaluation of rapid techniques for detecting SARS-CoV2 in asymptomatic and symptomatic patients consulting in emergency departments participating in the DEPIST-COVID trial by comparing the performance of rapid antigen tests (TRA) on saliva self-sampling compared to the reference technique RT-PCR on saliva self-sampling. The ancillary study will be carried out during the intervention strategy period of the DEPIST-COVID trial and/or during an extension of the study inclusion period.

This ancillary study is the subject of a protocol appended to the DEPIST-COVID study, currently being validated by REACTING/CAPNET.

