#### **6.3.5 Criteria for choosing tests**

The choice of test used is based on available data on sensitivity and specificity, on criteria for handling in the emergency department (storage, number of operations, time for reading, published experiments) and on the test supply capacities. These criteria led to the selection of the following tests with a CE marking:

1 - For patients with symptoms suggestive of respiratory infection: the test is based on a multiplex PCR technique detecting SARS-CoV-2 and all other community-acquired viral infections (Qiasat, Qiagen). This test involves performing a nasopharyngeal swab using a thin, flexible swab with a flocced nylon tip, inserting the swab into the test cassette and inserting it into the Qiasat automated PCR system, which performs all analytical steps. The result is available in 75 minutes. This test does not require any prior technical experience and can therefore be easily performed in an ED. In addition, the direct introduction of the swab into a cassette minimises the handling of an infectious sample and thus limits any risk of secondary contamination.

2 - For asymptomatic patients: an RT-LAMP (Abbott ID NOW, Abbott) test to detect the SARS-CoV-2 genome will be used.

It has several advantages:

- The technique is quick and easy to implement by staff not qualified in biology;
- It can be performed directly after sampling without handling infectious fluids;
- The result is available in less than 15 minutes, thus facilitating patient management;
- Single temperature genome amplification provides a simple and space-saving machine;
- The analytical performances (sensitivity and specificity) are close to those obtained with RT-PCR performed in a laboratory.

The RT-LAMP test is more sensitive than an antigen test and therefore more compatible with a diagnosis performed in a healthcare facility, while the antigen test is more suitable for mass testing in the outpatient department. Positive tests with the RT-LAMP technique performed in asymptomatic patients will not be confirmed by PCR.

This test is also performed using a nasopharyngeal swab. The swab is inserted into a cassette containing reagents that inactivate the virus by heating to 56°C. After inactivation, the viral genome is amplified by using isothermal nucleic acid amplification technology (NAAT) to detect the RNA-dependent RNA polymerase gene (RdRp) segment of the SARS-CoV-2. A real-time analysis

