## 13 STATISTICAL ASPECTS

### 13.1 Statistical justification for sample size

The estimate of the sample size is based on the comparison of 2 proportions (control group vs intervention group) using a Fisher's exact test, with, for the control group, a proportion of patients tested positive for SARS-CoV-2 among the enrolled patients of 0.1% and a proportion of 0.2% for the intervention group, bilateral  $\alpha=5\%$  and  $\beta=10\%$ .

The proportion of the control group was set using the incidence rate of SARS-CoV-2 among the general population in the Paris Metropolitan area. The incidence rate was 0.12% on 26/11/2020. It was estimated that the proportion of 0.10% was close to the baseline proportion of new SARS-CoV-2 positive cases among a flow of patients in the emergency department with usual screening practices. We estimated that the intervention would lead to a doubling of the proportion, i.e. 0.20%, which represents a substantial clinical gain. The correlations used are extracted from the DICI-VIH study (intra-cluster correlation:  $\rho=0.00014$ , correlation between-cluster:  $\rho_{12}=0.00009$ ). The calculation was performed with SAS software (version 9.4; SAS Institute, Inc., Cary, NC) and resulted in the need to enrol 104,000 patients, i.e. a total enrolment period of 2 months in 18 emergency departments (including 1 month intervention, 1 month control and wash-out).

Simulations were performed using different incidence rates and worst case scenario involving the largest number of patients to be enrolled, i.e. 104,000 patients. The 18 departments confirmed that they had ample potential for inclusion.

The calculation was performed in consultation with [name], INSERM, involved in the project and [name] from the biostatistics team of the CRU-East.

According to the feasibility data provided by the emergency departments and based on the experience of two research projects on testing in the emergency department, we estimate that approximately 16,700 tests (RT-LAMP and PCR multiplex) could be performed by nurses during the intervention period among 50,000 eligible patients, i.e. approximately 930 tests per site in 1 month and approximately 31 tests per day per site (19 RT-LAMP and 12 PCR multiplex per day).

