##### Primary endpoint analysis

The primary endpoint is the proportion of patients tested positive for SARS-CoV-2 amongst the flow of consulting adults. The denominator is a number of patients in the emergency departments (and not the number of tests performed).

Patients considered positive for SARS-CoV-2 will be those with a positive test result and whose SARS-CoV2+ status is not known. Patients considered non-positive for SARS-CoV-2 will be patients not tested, patients tested negative or with an undeterminate result and patients tested positive with a known SARS-CoV2+ status.

The primary analysis will be performed according to the intent-to-treat (ITT) principle. The primary outcome will be analysed using a generalised linear mixed model (Poisson distribution or any other distribution adapted to the data) with the centre as a random intercept and the strategy, the period and the period x strategy interaction as fixed effects. The incidence of SARS-CoV2 or the evolution of the epidemic over time will be taken into account if appropriate. Fixed variables could be added to the model if appropriate.

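### Unconfirmed RT-LAMP positives from asymptomatic screening count as new diagnoses, and that screening is added only under the intervention, so test error favours screening and no analysis quantifies it

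*Combined protocol and SAP*

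**What the plan says.** Section 6.3.5 of the protocol chooses RT-LAMP for asymptomatic patients, describes its sensitivity and specificity only as near those of laboratory RT-PCR, and adds: "Positive tests with the RT-LAMP technique performed in asymptomatic patients will not be confirmed by PCR".

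The final SAP, section 1.1, defines the case: "Patients considered positive for SARS-CoV-2 will be those with a positive test result and whose SARS-CoV2+ status is not known". The later page headed Changes to the analysis plan limits known status to less than 3 months and adds no confirmation step. Section 4.1 stresses that "the denominator is a number of patients in the emergency departments and not the number of tests performed", so each added positive raises the primary outcome directly.

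Section 13.1 plans "approximately 31 tests per day per site (19 RT-LAMP and 12 PCR multiplex per day", and sizes the trial on "a proportion of patients tested positive for SARS-CoV-2 among the enrolled patients of 0.1% and a proportion of 0.2% for the intervention group".

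Sections 3.2 and 4.2 describe the ancillary study differently. The first has it evaluating "in particular rapid antigen testing (RAT) and rapid molecular testing (RT-LAMP), compared to a reference technique, RT-PCR". The second has it "comparing the performance of rapid antigen tests (TRA) on saliva self-sampling compared to the reference technique RT-PCR on saliva self-sampling".

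Section 5.1 argues that open-label bias is limited because the outcome is objective. It does not discuss test error. Section 9 of the protocol and SAP 1.4 list virological confirmation data as a source, but no rule makes case status depend on it.

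**The concern.** The number of false positives depends on how many uninfected people are tested. The intervention consists of testing many more people, most of them uninfected. Errors in usual-practice tests arise in both periods and largely offset each other in a difference. Errors in the added RT-LAMP screening arise in one period only. The primary comparison can therefore move towards screening with no extra infection found, and this is a bias that a larger sample does not remove.

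The design makes this more than a formality, because the gain sought is very small in absolute terms: one extra case per thousand attenders. The asymptomatic yield, which SAP 1.1 compares with community positivity, carries the same error. No analysis in the plan shows how far either result depends on specificity.

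**Working it through.** **Inputs.** 16,700 nurse tests planned, 31 per site per day of which 19 RT-LAMP, rates of 0.1% and 0.2%, 104,000 patients, ρ = 0.00014 and ρ12 = 0.00009 (all section 13.1); 18 sites (5.2); one-month periods, taken as 30 days (5.1). Specificity is an assumption, varied from 99% to 99.9%.

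**1. The plan's own test volume.** 16,700 / 18 = 928 per site; 928 / 30 = 30.9 per day. This agrees with the stated 930 and 31.

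**2. Planned RT-LAMP tests.** 19 × 30 × 18 = 10,260. Intervention patients: 104,000 / 2 = 52,000. Planned gain: 0.10 point, or 52 cases.

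**3. Expected false positives.** (1 − specificity) × 10,260, then divided by 52,000. The few infected people among those tested are ignored.

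| Assumed specificity | False positives | Points added |
|---|---|---|
| 99.9% | 10.3 | 0.020 |
| 99.8% | 20.5 | 0.039 |
| 99.5% | 51.3 | 0.099 |
| 99.0% | 102.6 | 0.197 |

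The false gain equals the planned gain at 1 − 52 / 10,260 = 99.49%.

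**4. Chance of a false win.** Suppose there is no true gain and control is 0.1%. The design effect is 1 + (m − 1)ρ − mρ12 with m = 2,889, which is 1.144, so the effective size is 52,000 / 1.144, about 45,400 per strategy. In a two-sided 5% comparison of two proportions (normal approximation), the probability of significance in favour of screening is about 97% at 99.5% specificity, 40% at 99.8% and 14% at 99.9%. The design allows 2.5% in that direction. These figures treat all 10,260 tests as additional, so they are upper values for each specificity.

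**5. Delivered volume.** Table E1 lists 3,611 rapid molecular SARS-CoV-2 tests, which I take to be RT-LAMP, with 108 new diagnoses. Table H1 gives 1,859 intervention diagnoses.

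| Assumed specificity | False positives | Share of 108 | Share of 1,859 |
|---|---|---|---|
| 99.9% | 3.6 | 3% | 0.2% |
| 99.5% | 18.1 | 17% | 1.0% |
| 99.0% | 36.1 | 33% | 1.9% |

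Reducing the relative risk of 1.02 (Table I1) by the last column gives 1.02 × 0.998 = 1.02 to 1.02 × 0.981 = 1.00.

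**6. Community comparison.** Table J1 has 224 / 4,283 = 5.2% against 156,298 / 3,400,584 = 4.6%, difference 0.6 (0.01 to 1.3). The Miettinen-Nurminen interval reproduces this (0.63; 0.006 to 1.34). With one ED positive fewer, the lower limit is −0.02. With the expected RT-LAMP false positives removed at 99.9%, the difference is 0.55 (−0.07 to 1.25); at 99.5% it is 0.21 (−0.39 to 0.89). Community tests also have false positives, which would offset part of this.

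**The case against.** **The specificity is assumed.** This stands. A reader might infer that false positives alone would supply the whole planned gain. The documents do not support that, since it holds only at about 99.5% or lower; at 99.9% the share is one fifth. The plan's own figures lean against 99.5% for usual care. Section 2.3 gives 30 usual-practice tests per day per department, so 30 × 30 × 18 = 16,200 per period. At 99.5% these would yield 81 false positives, more than the 52 control cases planned. Usual-care specificity would have to exceed 1 − 52 / 16,200 = 99.7%. RT-LAMP is said to be close to that standard, but no number is given.

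**The asymmetry is partial.** This also stands. Usual practice could include RT-LAMP (sections 2.3 and 5.1), admitted patients were already screened (6.3.4), and Table C1 shows a rapid device in routine use in 9 of 18 departments. Some screening tests may have replaced usual-care tests. Moreover, the SAP models a log rate, and false positives common to both strategies pull a ratio towards 1. A correction must therefore cover both strategies.

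**Other inferences that do not hold.** Section 2.6 lists among expected events "the need to redo the test if it is invalid or read outside the time limits or if it must be confirmed". That is a general, conditional statement, and the specific rule in 6.3.5 does not contradict it. Centre 16's 2 / 353 in Table J2 cannot be used to bound RT-LAMP specificity, because its denominator is all nurse screening, multiplex PCR included. Nor can one conclude that a check of RT-LAMP was abandoned: the ancillary protocol is a separate document, and the questionnaire keeps fields for an antigen test and a transport-medium result. Only the difference between 3.2 and 4.2 is established.

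**The practical effect on the primary result is negligible.** This is correct for the delivered data.

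**Conclusion.** The point holds as a gap in the plan. A single unconfirmed RT-LAMP positive counts as a case, systematic RT-LAMP screening is added on one side only, and nothing quantifies the resulting bias. At the planned volume the false gain is about 0.02 to 0.20 points for assumed specificities of 99.9% down to 99%, against a target of 0.10, less any substitution for usual-care tests. Even at 99.9% the chance of a false win would be up to about 14%.

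A reader might infer that the reported primary result is compromised. It is not: at the delivered volume the expected false positives are at most about 2% of intervention diagnoses, and a relative risk of 1.00 to 1.02 leaves the null conclusion in place. The result that is sensitive is the asymptomatic yield. Up to a third of the 108 RT-LAMP diagnoses could be false at 99%, and the Table J1 interval excludes zero by so little that one positive decides it.

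All sizes rest on the assumed specificity range, on 30-day periods, and on every RT-LAMP test being additional.

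**What to change.** In final SAP section 1.1, pre-specify a quantitative bias analysis of the primary outcome. Re-estimate the strategy effect with expected false positives removed from both strategies, computed by test type and number of tests. Use a stated specificity range, for example 99% to 99.9% for RT-LAMP, with a separate range for PCR. If test type was not recorded for some usual-care tests, state the range used for them. Present it as a sensitivity analysis alongside the main result.

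Report the asymptomatic yield and the Table J1 comparison over the same kind of range, allowing for error in the community tests as well.

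Reconcile sections 3.2 and 4.2 on whether the ancillary study evaluates RT-LAMP. Whether positives should be re-tested in care is for the investigators and is not part of this point.

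The cost is a paragraph of SAP text and a short calculation, mainly on test counts already collected. The downside is a somewhat less favourable reported yield.

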### 6.3.6 Summary table of the research chronology

|                                                                                                                                                                                                                                                                                      | Intervention strategy                                                                                           | Control strategy                                                                                                        |
|--------------------------------------------------------------------------------------------------------------------------------------------------------------------------------------------------------------------------------------------------------------------------------------|-----------------------------------------------------------------------------------------------------------------|-------------------------------------------------------------------------------------------------------------------------|
| Information for patients by posters in all 18 emergency services (see addendum 3).
Distribution of an information sheet (see addendum 2) to patients meeting the inclusion criteria (> 18 years old) and collection of express consent.                                           | R                                                                                                               | R                                                                                                                       |
| Offer of a self-questionnaire (see addendum 2) to the patients included and able to complete the questionnaire. Agreement to participate in the study noted by the patient on page 1 of the questionnaire                                                                            | R                                                                                                               |                                                                                                                         |
| Offer of SARS-CoV-2 testing by the nurse or caregiver, regardless of the answer to the questionnaire                                                                                                                                                                                 | R                                                                                                               |                                                                                                                         |
| Nasopharyngeal sampling performed and result provided                                                                                                                                                                                                                                | R (In addition to usual practice, a nasopharyngeal sample RT-LAMP test is performed for asymptomatic patients.) | S
(usual practice based primarily on a SARS-CoV-2 diagnosis by PCR in hospitalised patients or symptomatic patients) |
| For patients tested SARS-CoV-2+ who have not completed questionnaires: collection of data from the DEPIST-COVID questionnaire during a telephone call.                                                                                                                               | R                                                                                                               | R                                                                                                                       |
| Assistance in completing a ComCor questionnaire from the Pasteur Institute in paper format (see addendum 6) (or online on the study site as possible), in order to facilitate the study of sociodemographic, behavioural factors and practices associated with SARS-CoV-2 infection. | R                                                                                                               |                                                                                                                         |

*S: usual practice in the context of Care; R: practice added by the Research*

